#### Cost effectiveness

Estimates of resource use and related costs for the delivery of Standing Practice In Rehabilitation Early after Stroke (SPIRES) will be measured through semi-structured interviews exploring time required for preparation for functional standing programme session. Duration of functional standing frame programme group session (total minutes) will be captured in the Case Report Form and will be compared with the duration (total minutes) of the usual physiotherapy (control) group.

### Management

#### Fidelity

Intervention fidelity, defined as adherent delivery of the intervention, will be evaluated using a trial-specific SPIRES checklist that outlined all components of the functional standing frame programme intervention, and usual physiotherapy control group to be completed by an independent observer (e.g. physiotherapist checked blood pressure, demonstrated, ensure foot sensors in situ and positioned safely, position participant in frame etc.).

#### Participant adherence

The tolerance/adherence of the functional standing frame programme to people who have had a severe stroke will be measured by tracking (i) total number of sessions completed; (ii) total number of minutes standing; (iii) total number of sit to stand repetitions; (iv) enjoyment; (v) effort; (vi) fatigue; and (vii) reasons for non-completion of sessions, as documented by treating physiotherapists in the Case Report Form.

#### Feasibility of outcome measures

The feasibility of the proposed outcome measures will be measured by the number of primary and secondary outcome measures completed and the ability to detect change in this patient group with severe mobility impairment.

#### Orthostatic Hypotension protocol

The feasibility and acceptability of the Orthostatic Hypotension protocol will be measured by the incidence of orthostatic hypotension, the number of incomplete sessions due to orthostatic hypotension and the number of participants who received pharmacological or non-pharmacological (abdominal binders) treatment.

### Safety

#### Intervention

Safety of the intervention will be measured by the number of adverse events and serious adverse events that occur during the SPIRES intervention period (e.g. falls, skin damage, infection, hospital admission, death). The treating physiotherapists are responsible for documenting any adverse events or serious adverse events.

#### Data collection

Safety during data collection will be assessed by the number of adverse events or serious adverse events that occurred during the follow-up period. The blinded assessors are responsible for recoding any adverse events that occurred during data collection.

More specifically the *objectives* related to the qualitative evaluation are to:Explore means by which the trial procedures (timing and mode of participant recruitment, information provision, methods of data collection for example timing and content of outcome measures) can be refined to maximise recruitment, retention and acceptability in the definitive trialExplore patient participants’ experience of the functional standing frame programmeExplore patient participants’ experience of being randomisedExplore patient participants’ reasons for, and experience of, withdrawing from the trialExplore relatives’ influence in participants’ decision to consent to participate, remain in the trial or provide assent for their relativeExplore physiotherapists’ attitudes, thoughts and feelings of implementing the intervention and whether they perceive a subsequent RCT to be achievableExplore physiotherapists’ attitudes, thoughts and feeling of the trial documentation and processes.

### Trial design

This is a pragmatic, multi-centre, parallel single-blinded two-armed feasibility RCT (Fig. 1).

**Fig. 1 Fig1:**
[figure not shown]
Trial flow chart. This figure represents the trial processes from assessing eligibility to data analysis

## Methods: participants, intervention and outcomes

### Trial setting

Three healthcare sites (with four Stroke Rehabilitation Units) will be involved in the trial, which is based in two counties in the South West Peninsula of England. A full list of trial sites is available via https://www.plymouth.ac.uk/research/spires.

### Eligibility criteria

#### Inclusion criteria for quantitative methods

The trial population will comprise individuals with a confirmed clinical diagnosis of new (first or recurrent) severe stroke, cerebral haemorrhage or infarct confirmed by consultant or computed tomography (CT) scan and leading to admission to the Stroke Rehabilitation Unit. Participants will be:Aged ≥ 18 yearsGraded as mRS 4 or 5 and/or National Institutes of Health Stroke Scale (NIHSS) ≥ 16 (severe or very severe stroke and unable to stand without support/mechanical aid and assistance of two people)Able to give informed consent or assent received from a consultee (see recruitment section)Conscious and responsive to verbal prompts.

#### Exclusion criteria for quantitative methods

Potential participants meeting any of the following criteria will be excluded from trial participation:Systolic blood pressure ≤ 100 mmHg or ≥ 220 mmHg at rest, lying or sittingOxygen saturation ≤ 87% with or without supplementary oxygen (e.g. severe acute/chronic cardiorespiratory disease)Resting heart rate of ≤ 40 or ≥ 110 beats per minute (e.g. cardiovascular instability)Temperature ≥ 38.5 degrees centigrade or ≤ 35 degrees centigradeOrthopaedic impairments which prevent full weight bearing in standingMalnutrition Universal Screening Tool score of ≥ 2, or deemed to be not meeting nutritional demands for therapeutic interventions by dieticianDocumented clinical decision for receiving end of life careUnstable coronary or other medical condition that is judged by the Principal/Chief Investigator (PI/CI) or clinical team to impose a medical risk to the patient by involvement in the trialAssessed functionally by specialist clinicians as being a risk to themselves or others due to their inability to follow non-verbal prompts or are behaving erraticallyImmobile and not weight bearing pre-strokeAdditional neurological deficits unrelated to the current or past stroke (e.g. peripheral neuropathy or multiple sclerosis), because these impairments are not related to the condition of interest)Weight of 115 kg or more, this is the weight limit on the standing framesBeing discharged out of county, e.g. admitted during holiday/visit to Cornwall or Devon because they would be unable to participate in follow-up assessmentsIf people are registered in another trial, the CI will be contacted to ensure there is no conflict between trialsNon-English speaking

#### Inclusion criteria for qualitative methods

##### Patient participants

Are able to use a range of communication methods including speech, gesture and/or writing as determined by the ConsentSupport Tool as well as other assessments determined appropriate by SLT based on the SRU, e.g. able to answer the questions in the patient-report outcome measures at the 3-week follow-up assessment visitAble to recall involvement in the study or study processes with or without prompts or aids (e.g. study documentation) as required.

##### Relative participants

Aged ≥ 18 yearsA family member/close friend of a participant registered in the SPIRES feasibility trialAble to provide written informed consent

##### Physiotherapist participants

Registered physiotherapist working on the Stroke Rehabilitation Unit for 3 or more days in each weekAble to provide written informed consent

### Intervention

The intervention will be delivered in the Stroke Rehabilitation Unit over a period of 3 weeks and will start as early as possible after randomisation to ensure that the treatment can be completed during the participant’s inpatient admission. The functional standing frame programme involves a maximum of 30 min using the standing frame (standing and repeated sit to stand) plus an additional 15 min to provide time for usual care physiotherapy, where participants may practise transfers, upper limb activities or activities chosen by participants or guided by physiotherapists. Participants will be asked to undertake the functional standing frame programme once a day, for a target of a minimum of 5 days per week which is aligned with the RCP Guidelines [34].

The initial frequency and duration of standing may vary according to physical capability as assessed by the treating physiotherapist. The aim is to progress standing time by 30% in each session, up to the maximum of 30 min. Each treating therapist will use their individual clinical reasoning when evaluating participants’ tolerance to standing and ability to tolerate incremental increases in standing duration. The associated Work Instruction (Additional file 1) contains specific details of how to implement this. Standing duration for each session will be recorded by the treating physiotherapist.

Participants will move from sitting to standing with aid of an electronic power lifter and a physiotherapist(s) and assistant as required. Foot sensors (integral to the frame design or customised) will record load through each leg when standing in the frame. The aim is for the foot sensors to be used as biofeedback to encourage equal weight distribution during quiet standing and sit-to-stand. Whilst standing, participants will be supported in the frame with straps at the ankle, knees, hips and trunk (if required). They will be encouraged to undertake progressive task-specific activities:Repeated sit-to-stand (aiming for 8–12 repetitions to facilitate strengthening)Table top games encouraging postural adjustments and use of upper limbsReductions in postural support, e.g. reducing hip and trunk strap tension during standing, elimination of electronic power lifter for sit-to-stand

Should participants improve to the extent where support from the standing frame is not required; then, unsupported standing/walking can be progressed outside of the frame to optimise physical recovery for the remainder of the 3-week intervention if indicated. Repeated sit to stand (8–12 repetitions) should, however, be continued throughout the 30 min session.

Physiotherapists will record activities undertaken during every session using a Physiotherapy Content Recording Tool (Additional file 2). This checklist is based on the Stroke Physical Therapy Intervention Tool [66] which provides a system for recording physiotherapy treatment for stroke patients and has been modified to reflect current clinical practice in a sub-acute rehabilitation setting. Recording physiotherapy interventions during sub-acute stroke rehabilitation will enable usual physiotherapy management to be defined and inform the subsequent main trial. This will include number of repetitions of sit-to-stand, activities undertaken whilst standing, reductions in postural support, duration of stand and activities undertaken in the 15 min of usual physiotherapy.

For the first three sessions (or longer if deemed appropriate by physiotherapists), blood pressure will be assessed both prior to and during the functional standing frame programme. This is based on the protocol used in the feasibility and safety testing of a very early rehabilitation trial [5]. If, when standing, a participant demonstrates OH (decrease in systolic blood pressure of ≥ 20 mmHg, or a reduction in diastolic blood pressure of ≥ 10 mmHg upon changing body position from a supine position to an upright posture, or sitting to standing) standing will be modified or, if required, ceased for that session. Details are contained in a trial-specific work instruction document.

If the participant demonstrates OH, a protocol to treat OH using non-pharmacological interventions will be implemented, in collaboration with the participant’s ward-based doctor. This protocol will provide details about application and monitoring of a compression garment and continued monitoring of blood pressure (available from corresponding author on request).

To standardise and optimise implementation of the functional standing frame intervention, all treating physiotherapists will be provided with face-to-face trial specific training by the CI and be included on the delegation log, authorised by the CI or PI. They will be provided with a link to the trial website, which will include videos demonstrating standing, examples of how to progress the programme using case scenarios, downloadable schema of suggested task-specific exercises/activities, advice on safety issues and “frequently asked questions”. It will also include trial details (e.g. background, rationale) and CI’s contact details. This will complement a trial-specific work instruction.

### Control (usual physiotherapy)

This is defined as routine physiotherapy stroke rehabilitation for 45 min per day (or as long as tolerated) for a target of a minimum of 5 days per week, which is aligned with RCP Guidelines [34]. There is no agreed upon definition of what constitutes usual physiotherapy; thus, there is likely to be variation in usual physiotherapy due to physiotherapists’ preferences, experience and training. Physiotherapists will record activities undertaken during every session using the Physiotherapy Content Recording Tool (Additional file 2) to enable description of usual physiotherapy across all four Stroke Rehabilitation Units. It will also capture any instances of protocol deviation where physiotherapists implement a standing frame programme with participants in the control group. The protocol, and face-to-face training sessions, advise physiotherapists not to change their usual physiotherapy practice.

It is expected, although not required, that the same physiotherapists will be delivering both interventions (e.g. implementing both the functional standing frame programme and usual physiotherapy). Clear instructions about content of the intervention and control group, combined with fidelity checking, aim to avoid any conflict. However, potential for bias is acknowledged, and therefore, a stepped wedge cluster RCT [28] may be considered for the future main trial. This would allow every site (cluster) to deliver both the control and the intervention, with every cluster switching from control to the intervention, but at different time points.

### Standardisation of the intervention

Treating physiotherapists from each of the three healthcare sites will perform the interventions as part of their clinical role; the CI and a blinded assessor (employed specifically for one site) will undertake the assessments.

Use of standing frames is incorporated within undergraduate physiotherapy training and is a recognised core skill for neurological physiotherapists. To standardise and optimise implementation of the intervention, treating physiotherapists will receive face-to-face training and an information pack. This includes a written template of what is required to be undertaken within each session (Figs. 2 and 3) and a link to the trial website.

**Fig. 2 Fig2:**
[figure not shown]
Flow chart 1. Procedure for implementing the functional standing frame programme whilst monitoring BP. This figure represents the procedures for the functional standing frame programme intervention. This first flowchart encompasses the monitoring of blood pressure to ensure participant is safe to continue with the intervention

**Fig. 3 Fig3:**
[figure not shown]
Flowchart 2. Procedure for implementing functional standing frame programme when OH stabilised. This second flowchart provides a diagramatical representation of procedures to follow for the functaional standing frame programme for patient participants who have been deemed to have stable blood pressure

Treating physiotherapists and the assessors are required to record any deviations from the protocol on a Protocol Deviation form.

Inter-rater reliability will be assessed for the blinded assessors on all outcome measures (both primary and secondary).Proposed primary outcome measures

The proposed primary outcome measure assesses functional ability in performing activities of daily living. Functional ability was identified as being important and a priority for people with severe stroke and their relatives during discussions in the development of this feasibility trial.

The Barthel Index of Activities of Daily Living (BI) [41] is frequently used in stroke clinical trials, although was not designed specifically for clinical trials or the stroke population. The BI rates a person’s degree of independence performing functional self-care (feeding, grooming, bathing, etc.) and mobility activities (transferring in/out of bed/chair, walking, etc.). A major limitation of the BI is its floor effect [51], and as a result, it has limited ability to detect change at extremes of ability, making it less discriminating in severe stroke [55].

This feasibility trial provides the opportunity to investigate whether an alternative functional outcome measure is more sensitive to change in people with severe stroke. Therefore, the Edmans Activities of Daily Living Index for Stroke Patients [20] will also be used. This measure has cover all the categories included in the BI; however, the response categories are independent, supervision, help of one and help of two, as opposed to the BI responses which are only dependent or independent for each item assessed.2)Proposed secondary outcome measures

*Blood pressure in lying and sitting* to determine presence of orthostatic hypotension using sphygmomanometer: Orthostatic hypotension is a decrease in systolic blood pressure of ≥ 20 mmHg, or a reduction in diastolic blood pressure of ≥ 10 mmHg upon changing body position from a supine position to an upright posture, or sitting to standing [39]. This feasibility trial will record the incidence of OH and whether OH limits participation in the functional standing frame intervention.

*Control of trunk* using Trunk Control Test [18]: The Trunk Control Test has demonstrated construct and predictive validity [22] and concurrent validity and interrater reliability [12].

*Knee extension muscle strength* (left and right) using hand held dynamometer [33, 52]: Knee extensor strength is strongly correlated to common daily functional activities such as the ability to sit to stand, stand and walk in people with sub-acute stroke [33]. It is reliable in measuring lower limb strength in people with stroke (ICC = 0.88–0.98) [52].

*Length of hip flexors, hamstrings and ankle plantarflexors* (left and right) using manual universal goniometer [7]: Passive range of movement of these muscles will be measured on both lower limbs. Intra-rater reliability using goniometry to measure ankle plantarflexor length was moderate to good (ICC 0.719–0.892) and inter-rater reliability was moderate (ICC 0.725–0.741) in people with stroke.

*Muscle tone in hip adductors, hamstrings and ankle* (left and right) using Modified Ashworth Scale [24]: The Modified Ashworth Scale shows good inter-rater reliability hip and knee (weighted kappa = 0.82) and ankle (weighted kappa = 0.74); moderate intra-rater hip (weighted kappa = 0.45); good intra-rater reliability for knee (weighted kappa = 0.62) and very good for the ankle plantarflexors (weighted kappa = 0.85) people with stroke [25].

*Mood* using Patient Health Questionnaire (PHQ-9) [72] or Stroke Aphasia Depression Questionnaire-10 (SADQ-10) for participants who have aphasia [61]: PHQ-9 shows good sensitivity (78%) and specificity (96%) for any depression diagnosis regardless of age, gender or ethnicity [72] and the SADQ-10 shows good internal consistency (Cronbach’s alpha = 0.80 and a split-half reliability of *r* = 0.81) [61].

*Health-related quality of life* using Stroke and Aphasia Quality of Life Scale-39 [30] and the EuroQol Group 5 Dimensions, 5 Levels (EQ-5D 5L) [29]: The Stroke and Aphasia Quality of Life Scale-39 has high internal reliability (alpha = 0.74–0.94) and test re-test reliability is also good (ICC = 0.89) [30]. However, it is unknown whether it is feasible for people with severe stroke to use this outcome measure due to communication and cognitive impairments. The EQ-5D-5L shows moderate responsiveness to change (SRM = 0.63) and a minimally clinically important difference of 0.10 [11].

*Fatigue* using a Visual Analogue Scale (Additional file 3) to enable people with aphasia to also rate their level of fatigue [36].

### Qualitative evaluation

Qualitative methodology will enable exploration of the thoughts, feelings and experiences of trial participants, their relatives and treating physiotherapists/PIs. Stratified purposive sampling will be used to achieve maximum variation to request semi-structured interviews with 16 participants (approximately six in the functional standing frame group, six in the usual physiotherapy group and four people who decline to participate or withdraw), eight relatives and eight treating physiotherapists. A combination of face-to-face, telephone or Skype will be offered for the interviews to inform the most appropriate method for the definitive main trial. The aim of the qualitative interviews is to address several uncertainties or unknowns including recruitment, retention, practical implementation of the intervention, acceptability/tolerance of the intervention, informed consent, and suitability and acceptability of outcomes measures to inform the design and implementation of the definitive main trial.

People with mild to moderate aphasia will be interviewed as it is important to seek the perspectives and experiences of people with aphasia due to its high prevalence in people with stroke. However, people with severe aphasia (unable to complete the patient-report outcome measures) will be unable to participate due to inability to comprehend and/or express their views and will therefore be excluded.

All physiotherapists involved in delivering the trial (PIs and treating physiotherapists) will be invited to a focus group at the end of the recruitment period to discuss their experiences of delivering the trial (participant recruitment, documentation, delivery of the intervention, etc.) to further evaluate and improve procedures for the definite trial. All interviews and focus group will be digitally recorded and transcribed verbatim.

### Sample size

As a feasibility trial, a formal sample size calculation based on considerations of power is not appropriate; this trial is not statistically powered to detect between-group clinically meaningful differences in a primary outcome. One of the objectives of this trial is to provide robust estimates of the likely rates of recruitment and follow-up, as well as provide estimates of the variability of the proposed primary and secondary outcomes to inform sample size calculations for the planned definitive trial. There is no consensus on the recommended number of participants required for a feasibility trial, with published “rules of thumb” ranging from 20 to 70 or more participants, when the planned primary outcome is of a continuous nature. A recent paper recommended a feasibility trial sample size should recruit 25 participants per allocated group, if the planned definitive trial will have a two-arm parallel group design, with 90% power and two-sided 5% significance level, to detect a “small” standardised effect size [71]. Therefore, this feasibility trial aims to recruit 50 participants in total.

A target sample size of 50 patient participants will allow the follow-up rate to be estimated to within ± 15%. The follow-up rate at 12 months is estimated to be 70%, which would provide follow-up outcome data on a minimum of 35 participants across both allocated groups and three sites.

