### Determining progression to the full trial

Progression to a full trial application will occur if minimum success criteria are achieved in key feasibility aims and objectives, and/or if solutions can be identified to overcome any issues. These criteria will be finalised in discussion with the Trial Steering Committee, but are likely to include a minimum of:70% recruitment of the intended 50 patient participants within the 13-month recruitment window80% of consented patient participants randomised to the intervention group engaging with and adhering to a minimum of five session per week during the three-week SPIRES intervention80% completion rate of outcome measures (including follow-up)

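### The 35 participants described as a minimum with 12-month data is the expected number if all 50 are recruited, not a floor

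*Protocol article*

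**What the plan says.** The Sample size section of the protocol article sets the target from a published recommendation: "A recent paper recommended a feasibility trial sample size should recruit 25 participants per allocated group", leading to "Therefore, this feasibility trial aims to recruit 50 participants in total". The next paragraph gives the precision expected for the follow-up rate: "A target sample size of 50 patient participants will allow the follow-up rate to be estimated to within ± 15" per cent. It continues: "The follow-up rate at 12 months is estimated to be 70" per cent, and says that this rate "would provide follow-up outcome data on a minimum of 35 participants across both allocated groups and three sites".

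The same section gives the purpose of the data: to estimate recruitment and follow-up rates, and the variability of the proposed outcomes, for sizing the definitive trial.

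The section on determining progression to the full trial lists criteria still to be finalised with the Trial Steering Committee. One of them is "70% recruitment of the intended 50 patient participants within the 13-month recruitment window", which is 35 people recruited.

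**The concern.** A minimum is a number that the trial will not fall below. The text derives 35 by applying an estimated rate to the full target, which gives an average outcome. Nothing in the section presents 70% as a lower bound, and nothing guarantees all 50 recruits.

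The figure tells the reader how much 12-month information the trial can be relied on to deliver. If 35 is taken as the worst case, the lower end of what may be available is hidden. A funder or steering committee could then think the 12-month estimates of variability and follow-up are more secure than they are.

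The number 35 also appears in two roles. It is 70% of 50 followed up in the sample size section, and 70% of 50 recruited in the progression section. If only 35 were recruited, 35 with 12-month data would need no loss at all.

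**Working it through.** **Inputs**
- Planned total: N = 50 (Sample size).
- 12-month follow-up rate: p = 0.70, given as an estimate (Sample size).
- Number per group: 25 (Sample size), assuming an even split.
- Provisional recruitment threshold: 0.70 x 50 = 35 (Determining progression to the full trial).

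**1. Reproduce the plan's figure.** Expected number with 12-month data = N x p = 50 x 0.70 = 35.0. This matches exactly, so 35 is a mean. It is also the binomial median.

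**2. Chance of falling short with full recruitment.** Let X be the number with 12-month data, X ~ Binomial(50, 0.70).
- P(X >= 35) = 0.569.
- P(X < 35) = 1 - 0.569 = 0.431.
- 2.5th and 97.5th percentiles: 28 and 41.
- 5th percentile: 30.

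**3. Sensitivity to the true rate, all 50 recruited**

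| True rate | Expected number | P(at least 35) | P(fewer than 35) |
|---|---|---|---|
| 60% | 30.0 | 0.10 | 0.90 |
| 65% | 32.5 | 0.28 | 0.72 |
| 70% | 35.0 | 0.57 | 0.43 |
| 75% | 37.5 | 0.84 | 0.16 |
| 80% | 40.0 | 0.97 | 0.03 |

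Only 70% comes from the protocol; the other rates are assumptions that show the range. Even if 70% were a cautious guess and the truth were 75%, the count would fall below 35 about one time in six.

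**4. Per group.** 25 x 0.70 = 17.5, so about 17 to 18 per group at 12 months.

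**5. Recruitment at the provisional threshold.** 35 x 0.70 = 24.5, so about 24 to 25 in total.

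**6. Check of the stated precision.** The 95% half-width for the follow-up rate is 1.96 x sqrt(p(1 - p)/50). At p = 0.70 it is 1.96 x sqrt(0.21/50) = 0.127, or 12.7 points. At p = 0.50 it is 13.9 points. Both lie within the stated 15 points, so that sentence is correct for 50 participants.

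**7. Effect on the precision of a standard deviation.** The 95% interval for a pooled SD, as a multiple of the estimate, runs from sqrt(df / chi-square 97.5th percentile) to sqrt(df / chi-square 2.5th percentile), with df = n - 2.
- n = 50: 0.83 to 1.25.
- n = 35: 0.81 to 1.32.
- n = 28 (lower end of the range in step 2): 0.79 to 1.37.

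**The case against.** The strongest reply is that this turns on one word. The trial disclaims a formal power calculation, and the loss from 50 to 35 is stated openly beside the target. No procedure, analysis or recruitment target depends on the word *minimum*, and step 7 shows that the SD interval widens only modestly. All of that stands, and it limits the weight of the point. It does not make 35 a floor.

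A reader might go further in four ways that the document does not support.

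- *That the 25-per-group rule is broken because only 17 to 18 per group remain at 12 months.* The rule is quoted as a number to recruit, and 50 meets it. The protocol never claims 25 per group at 12 months. Whether the cited paper means recruited or analysable participants cannot be settled from the text.
- *That the precision claim is wrong or contradicts the 35.* It describes how closely the follow-up rate will be estimated with 50 participants, and it is correct there. It is not a tolerance around 70% to be converted into a range of counts.
- *That the plan accepts 35 recruits as its sample size.* The threshold is provisional, sits among criteria for progression, and is not a rule for stopping recruitment. Another provisional criterion beside it is 80% completion of outcome measures. If that is read as 80% of 35 recruits, it gives 0.80 x 35 = 28, still below 35. The figure of 24.5 is therefore a scenario, not a prediction.
- *That the definitive trial will be sized on a weak 12-month SD and should use an upper confidence limit instead.* The article names no primary time point among its follow-up visits, says that existing literature will also be used, and does not commit to the point estimate. That choice belongs to the later trial's design.

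**Conclusion.** The point holds in a narrow form. The sample size section labels an expected value as a minimum. With all 50 recruited and a true 12-month rate of 70%, there is a 43% chance of fewer than 35 participants with data, and the central 95% range is 28 to 41. With 35 recruited, the expected number is 24 to 25.

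These figures treat participants as independent with a common follow-up probability. They do not include uncertainty in the 70% itself or shared effects within the sites, and either would widen the range. The figure of 17 to 18 per group assumes an even split, which minimisation favours but does not guarantee.

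This is a wrong statement about what the sample size delivers and should be corrected. It does not show that the target of 50, the quoted 25 per group or the stated precision is wrong.

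**What to change.** In the Sample size section, replace the phrase giving a minimum of 35 with wording to this effect: *an expected 35 participants (about 17 to 18 per group; 95% range 28 to 41) if all 50 are recruited, and about 24 to 25 if only 35 are recruited.*

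This changes wording only. It needs no extra participants and no change to the recruitment target, progression criteria or analysis. The cost is a less favourable stated figure.
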